### Statistical issues

3.1

We defined two main groups of vascular surgical procedures with groin incisions that carry different infection risk profiles. Infection rates and other statistics stem from a review of data collected during 2014–2016 after elective open lower limb revascularization procedures at Jönköping County Hospital [15]. Reanalysis of this material was performed in order to retrieve data after elective procedure outcomes only.

In about 95% and 5% of cases, *TEA* will be performed through a unilateral respective bilateral inguinal approach. This type of procedure carries an SSI risk of 22.2%. Mortality in this group was 13.9% at one year. In about 90% and 10% of cases, bypass will be performed through a unilateral respective bilateral inguinal approach. The bypasses incorporating both groins are aorto-bifemoral or femoro-femoral bypasses. This type of procedure had an SSI rate of 41.1%. A few bypasses will not have an inguinal incision (operation for popliteal artery aneurysm). Mortality in this group was 8.9% at 1 year.

### Sample size calculation

3.2

We used G*Power 3.1 [19] software for power calculations.

We first conducted power calculations, 80% power at 5% significance level, assuming all cases were either unilateral (Fisher's exact test, sample size n1) or bilateral (McNemar's test, sample size n2). Central to the power analysis of bilateral cases is the proportion of discordant pairs, meaning the proportion of outcomes that differ between the two sides, e.g. the proportion of cases where an infection is observed on one but not the other side. Assuming for instance a SSI rate reduction from 20% to 8% in bilateral TEA procedures, the proportion of cases in which the infection outcome is different in the right and left groin wounds respectively has to be at least as large as the difference between the current SSI rate with the standard dressing and the predicted SSI rate with the PICO™ system (20%–8% = 12%). The proportion of discordant pairs needs to be larger than the difference in SSI rate to account for the possibility that some patients may suffer from an infection on the PICO™ dressing side and not the standard dressing side.

After having determined the required sample sizes for the uni- and bilateral scenarios individually, the final sample size required was calculated as a weighted average based on the expected proportion (p) of unilateral and bilateral operations [15**]** (Table 1).**TEA** Previous data indicated an inguinal SSI rate after TEA without bypass of 22.2% when using the standard dressing. For bilateral cases, we estimated the proportion of discordant pairs to be 20%. Assuming all cases are either unilateral or bilateral, and a reduction in SSI rate from 20% to 8%, yields n1 = 284, and n2 = 210, respectively. Among all TEA cases, 95% are assumed to be unilateral (i.e. p1 = 0.95) (Table 1):n = p1 *n1 + (1 - p1) *n2. n = 0.95 * 284 + 0.05 * 210 = 280

**Table 1 tbl1:**
[figure not shown]
Characteristics of the two main types of procedures studied.

Taking into account the previously identified 1-year mortality of 13.9%, yields a mortality-corrected sample size of n = 325 (280/(1–0.139)).

In an attempt to adjust for other types of “loss to follow-up” such as missing data and re-operations on the respective side, we added an additional 10% (33 cases) resulting in a total sample size of 358. **BYPASS** Previous data indicated an SSI rate after bypass of 41.1% when using the standard dressing. Assuming all cases are either unilateral or bilateral, and a reduction in SSI rate from 40% to 15% with a proportion of discordant pairs of 40% in bilateral cases yields n1 = 112 and n2 = 93, respectively. Among all bypass cases, 90% are assumed to be unilateral (i.e. p1 = 0.90) **(**Table 1**)**:n = p1 *n1 + (1 - p1) *n2. n = 0.90 * 112 + 0.10 * 93 = 110

The 1-year mortality in this group was 8.9%, yields a mortality-corrected sample size of n = 121 (110/(1–0.089)). To adjust for other types of “loss to follow-up”,we added an additional 10% (12 cases) resulting in a total sample size of 133.

## Statistical analysis

4

We will conduct a descriptive analysis of background data such as comorbidities, procedure-related risk factors and different operation techniques. Important differences will be accounted for in a sensitivity analysis.

The study involves both uni- and bilateral inguinal incisions. Unilateral incisions are treated with either standard or NPWT dressing according to the randomization result and analyzed with *Fisher's exact test for independent samples*. In case of bilateral incisions, one is randomly designated to either standard or NPWT treatment group, the other by default to the alternate treatment group. It is important to recognize that the outcomes in the treatment groups in this scenario will not be independent of one another and will therefore be analyzed with *McNemar's test for paired data*. The advantage of the bilateral design is that all patient-related risk factors, such as comorbidities and hygiene factors, are exactly the same in both treatment groups and patients serve as their own control. The bilateral design thus decreases the required group size at a fixed level of statistical power, as can be seen from the assessments of n1 and n2 above. The obtained p-values from the uni- and bilateral analyses will subsequently be combined to an overall p-value using *Fisher's method of combining p-values* [20]. The e logarithm of the two p-values are calculated, summed, and multiplied with 2, resulting in a chi-square distribution with four degrees of freedom and a corresponding combined p-value (Excel sheet calculation). By using *McNemar's test* for analysis of bilateral incisions, we avoid the problem of “clustering” due to statistical dependent observations which if not accounted for would lead to too small standard errors and p-values [21].

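### The 80% power is claimed for two separate tests; the Fisher combination actually planned has about 56–60% power with exact McNemar, or 67–70% with uncorrected McNemar

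*Protocol article*

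**What the plan says.** Protocol article, Sample size calculation: "We first conducted power calculations, 80% power at 5% significance level" are run as if all cases were unilateral (Fisher's exact test, n1) or all bilateral (McNemar's test, n2). For TEA, "a reduction in SSI rate from 20% to 8%, yields n1 = 284, and n2 = 210, respectively". These are averaged by the expected case mix: "n = 0.95 * 284 + 0.05 * 210 = 280". Bypass is treated in the same way (40% to 15%, 40% discordant pairs, n1 = 112, n2 = 93, 90% unilateral), which gives 110. Allowances for one-year mortality and a further 10% raise these to 358 and 133, which the Abstract counts as groin incisions.

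Statistical analysis: unilateral incisions go to Fisher's exact test and bilateral ones to McNemar's test. "The obtained p-values from the uni- and bilateral analyses will subsequently be combined to an overall p-value using" Fisher's method, described thus: "The e logarithm of the two p-values are calculated, summed, and multiplied with 2", and referred to a chi-square distribution with four degrees of freedom. The same section says "The bilateral design thus decreases the required group size at a fixed level of statistical power", pointing to n1 and n2.

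**The concern.** A weighted average of two sample sizes, each right for its own test, does not give the power of a third test. Fisher's method gives the bilateral p-value the same weight as the unilateral one, although bilateral cases are 5% (TEA) or 10% (bypass) of the total. With so few pairs the McNemar p-value is seldom small and often equals 1, and it then drags the combined result away from significance.

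This is the confirmatory comparison in both procedure groups. If its power is well below 80%, a true effect of the planned size is more likely to be missed than the article says.

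**Working it through.** **Inputs.** All are from Sample size calculation: TEA 20% v 8%, 20% discordant, 95% unilateral, 280 evaluable; bypass 40% v 15%, 40% discordant, 90% unilateral, 110 evaluable. The discordant split follows from sum and difference: TEA 16% and 4%, bypass 32.5% and 7.5%. Assumptions: equal unilateral arms, two-sided 5% tests, and McNemar p = 1 when no pair is discordant.

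**The plan's own figures.** Full enumeration of the two-sided Fisher's exact test gives 80.2% power at 142 per arm (n1 = 284) and 80.8% at 56 per arm (n1 = 112). For McNemar, pairs = [1.96√ψ + 0.842√(ψ − d²)]²/d², with ψ the discordant share and d the difference:
- TEA (ψ = 0.20, d = 0.12): 106.6 pairs, or 213 incisions (stated 210).
- Bypass (ψ = 0.40, d = 0.25): 47.8 pairs, or 95.6 incisions (stated 93).

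So n2 counts incisions, and the weighted averages of 280 and 110 reproduce. The component sizes are sound for the component tests.

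**Number of pairs.** If the bilateral share is of incisions: TEA 0.05 × 280 = 14 incisions = 7 pairs; bypass 0.10 × 110 = 11 incisions, about 5 pairs. If it is of patients: TEA 280/1.05 ≈ 267 patients, about 13 pairs; bypass 110/1.10 = 100 patients, 10 pairs.

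**Power of the planned test.** I crossed every unilateral 2×2 table with every discordant split and rejected when −2(ln p1 + ln p2) ≥ 9.488.

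| Group (per arm + pairs) | Unilateral test alone | Combined, exact McNemar | Combined, uncorrected McNemar |
|---|---|---|---|
| TEA (133 + 7) | 77.3% | 56.6% | 66.8% |
| TEA (127 + 13) | 74.9% | 58.5% | 69.5% |
| Bypass (50 + 5) | 75.8% | 56.1% | 68.0% |
| Bypass (45 + 10) | 69.5% | 59.4% | 70.4% |

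Continuity-corrected McNemar behaves like the exact test. Slightly different splits of the same totals stay within 56.1–60.1% (exact).

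**Mechanism.** With x = p1·p2, the combined p-value is x(1 − ln x). If p2 = 1, the unilateral p-value must be at most exp(−9.488/2) = 0.0087. A unilateral p of 0.02 then becomes 0.02 × (1 + 3.912) = 0.098. Exact McNemar needs at least 6 discordant pairs, all one way, to fall below 0.05. Its p-value equals 1 in 72.5%, 48%, 56% and 28% of trials in the four rows above.

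**Type I error.** With the control rate in both arms, the combination rejects in 0.7–1.1% of trials (exact McNemar) and in about 2% (uncorrected).

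**Direction.** Take a unilateral benefit at p = 0.03 and five discordant pairs all showing harm, p = 2 × 0.5⁵ = 0.0625. Then x = 0.001875 and the combined two-sided p is 0.001875 × (1 + 6.279) = 0.014.

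**Stratified alternative.** The Cochran-Mantel-Haenszel statistic is [(O − E) + (b − c)/2]² / [V + (b + c)/4]. O, E and V are the observed count, hypergeometric mean and variance of the unilateral table, and b and c are the discordant counts. Without the unilateral table it reduces to (b − c)²/(b + c), which is McNemar's test. In the four configurations its power is 79–80% with continuity correction (type I error 3.1–3.5%) and 84–85% without (4.8–5.0%).

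**The case against.** **The low figure depends on a choice the article does not make.** This stands. The 56–60% needs exact or continuity-corrected McNemar; the uncorrected statistic gives 67–70%. A reader might infer that the trial would miss its planned effect in about 42% of cases. That is one branch only, and the documents do not fix it.

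**280 and 110 may be too few.** The Endpoints section sets 90 days, while the inflation uses one-year mortality, so more incisions may be evaluable. If only about 10% are lost (about 324 and 122 incisions), power is about 63–69% with exact McNemar and 75–78% with uncorrected. With no losses (358 and 133) it is about 69–75% with exact and 80–83% with uncorrected McNemar. Only this last case reaches the stated power, and it uses up the whole allowance for losses.

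**The remark on bilateral design is not wrong.** A reader might infer that the combined test refutes it. It compares n1 with n2 (210 against 284, 93 against 112), where it holds, and says nothing of the combination. Nor does the combination always cost power: with about 10 bypass pairs and uncorrected McNemar it has 70.4%, against 69.5% for the unilateral test alone.

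**Not all of the shortfall comes from the combination.** The unilateral subset is smaller than n1, which accounts for about 3–5 points in TEA and 4–11 in bypass. The fair comparator for exact tests is the continuity-corrected stratified test (79–80%), not the uncorrected one.

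**The method respects pairing and controls type I error.** It does; it is inefficient, not anti-conservative. The missing minus sign is a wording slip, since the method is named and the degrees of freedom are right. An effect estimate may properly be left to the full protocol or analysis plan.

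**Conclusion.** The point holds in conditional form. The article claims 80% power for tests that are only components of the planned analysis, and calculates none for the combined test. At the evaluable numbers to which the claim applies, and under the plan's own rates and discordance, the combined test has about 56–60% power with exact McNemar and about 67–70% with uncorrected McNemar, in both procedure groups.

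With exact McNemar, the combination does worse than discarding the bilateral patients altogether (70–77%). With the uncorrected version this is also so, except at about 10 bypass pairs. The blindness to direction applies if the component p-values are two-sided: the article does not state their sidedness, but n1 reproduces only as two-sided.

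It should not be read as saying that the test is invalid or that false positives are inflated; the type I error is about 1–2%.

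**What to change.** Replace Fisher's combination by one Cochran-Mantel-Haenszel test per procedure group, with all unilateral incisions as one stratum and each bilateral patient as a stratum. State whether a continuity correction is used. Pairing is kept, opposite effects offset each other, and a common odds ratio with confidence interval can come from the same strata. The cost is a change of analysis wording, with no extra patients or data. The article says that it was published before enrollment was complete and before analysis, so the change could be made and dated before outcomes are compared by dressing.

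If Fisher's method is kept: name the McNemar version, restate the power as about 56–70% depending on that version, combine one-sided p-values in the same direction, and write the factor as −2. The 56–70% was computed with two-sided p-values and should be recomputed for the one-sided form. Keeping 80% power with the present two-sided combination and exact McNemar would instead need about 410 evaluable TEA incisions and 155–160 bypass incisions, against 280 and 110.

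### The combined test statistic for the overall SSI p-value is printed without its minus sign, so the formula as worded contradicts the method it names and cannot be applied literally

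*Protocol article*

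**What the plan says.** The primary endpoint is the SSI rate (protocol article, section 2.2). Under section 4, Statistical analysis, unilateral incisions are compared with Fisher's exact test and bilateral incisions with McNemar's test. The two p-values are then merged into an overall p-value by "Fisher's method of combining p-values", with a literature reference.

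The next sentence spells out the calculation: "The e logarithm of the two p-values are calculated, summed, and multiplied with 2, resulting in a chi-square distribution with four degrees of freedom". It adds that this yields the combined p-value and that the work is done in an Excel sheet. The article prints no other formula for the overall p-value and no worked example.

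**The concern.** The sentence multiplies the summed logs by 2, not by -2. A p-value lies between 0 and 1, so its natural log is zero or negative, and twice the sum is too. A chi-square variable cannot be negative. The sentence therefore conflicts with the method named just before it and with the reference distribution that it gives itself.

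The place matters. This sentence describes how the overall p-value is obtained, and that p-value carries the comparison on the primary endpoint. A spreadsheet built strictly from the printed words would return a combined p-value of 1 for any data, or possibly an error.

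**Working it through.** **Inputs.** The printed rule and the named method both come from section 4. The article gives no numerical combined p-value to reproduce, so the p-values below are illustrative.

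**1. What can be confirmed.** Under the null hypothesis, if p is uniform on (0, 1), then -2 ln p is chi-square with 2 degrees of freedom. Unilateral and bilateral cases are different patients, so the two p-values are independent and the degrees of freedom add: 2 + 2 = 4. The article's four degrees of freedom are right, but they belong to -2(ln p1 + ln p2).

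**2. Sign of the printed statistic.** For 0 < p ≤ 1, ln p ≤ 0. So 2(ln p1 + ln p2) ≤ 0, with equality only when both p-values are 1. A chi-square variable with 4 degrees of freedom has mean 4 and takes no negative values. The probability that it exceeds a value at or below zero is 1.

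**3. Tail formula.** For x ≥ 0, the upper tail of chi-square with 4 degrees of freedom is exp(-x/2) × (1 + x/2). The 5% critical value is 9.488.

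**4. Example with p1 = 0.01 and p2 = 0.5.**
- As printed: 2 × (-4.605 - 0.693) = -10.60, upper-tail p = 1.
- With the minus sign: +10.60, p = exp(-5.298) × (1 + 5.298) = 0.005 × 6.298 = 0.031. This exceeds 9.488 and is significant at 5%.

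**5. Further examples.**

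| p1, p2 | As printed | Upper-tail p | With -2 | Upper-tail p |
|---|---|---|---|---|
| 0.05, 0.05 | -11.98 | 1 | 11.98 | 0.0175 |
| 0.001, 0.01 | -23.03 | 1 | 23.03 | 0.000125 |
| 1, 1 | 0 | 1 | 0 | 1 |

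Stronger evidence makes the printed statistic more negative, while its upper-tail probability stays at 1. The sentence does not name the tail. The lower tail would not help: the probability below a value at or under zero is 0 for any data.

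**The case against.** The strongest reply is that nobody could mistake the intended test. The method is named and referenced, and the stated chi-square distribution is true only of -2 times the sum. All three indications lead to one standard calculation, and one line of prose has lost a sign. A result of 1 for every dataset, or a spreadsheet error, would expose the slip at once. The sheet itself is not shown, and nothing suggests that it repeats the mistake. All of this stands, and it limits the practical consequence. It does not make the printed sentence correct.

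Three stronger readings are tempting, and the documents do not support them.

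- **The trial has 0% power where 80% was promised.** Zero rejection is a property of the literal wording only. The sample size section says "We first conducted power calculations, 80% power at 5% significance level, assuming all cases were either unilateral" or all bilateral. The 80% belongs to those two separate scenarios, and no power is stated for the combined test. How much power the correctly signed test has at the planned sizes is a different question.
- **The formula would have to be changed after the data are seen.** Restoring the sign that the named method requires leaves the analyst no choice to make, so it is not a data-driven change. It can also be done now.
- **The spreadsheet is wrong.** The article mentions the sheet but does not show its content.

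**Conclusion.** The point holds as an error in a stated rule. The formula for the overall SSI p-value lacks its minus sign, contradicts both the named method and its own reference distribution, and cannot give significance if followed to the letter. In the worked example the difference is p = 1 against p = 0.031.

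The realised harm is probably small, because the intended test can be recovered without ambiguity. No conclusion about power, sample size or the validity of the intended analysis follows.

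This rests on two assumptions. The combined p-value is read as the upper-tail probability, as Fisher's method requires. The missing sign is also taken to be in the article rather than lost when the PDF was read; the minus in the -80 mmHg pressure setting (section 2.7) survived, and the multiplication is described in words.

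**What to change.** In section 4, state that the natural logs of the two p-values are *summed and multiplied by -2, and that the combined p-value is the upper-tail probability of chi-square with 4 degrees of freedom*.

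Before the analysis, enter p-values of 0.01 and 0.5 in the Excel sheet and confirm that it returns 10.60 and p = 0.031.

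The cost is one corrected sentence and one spreadsheet check. Patients, data, sample size and the intended analysis are unaffected.

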## Discussion

5

Vascular surgery with inguinal incisions carries a significant risk for SSI. Extensive need for incisions in the lower limb increases the risk of SSI. Incisional NPWT could be an important tool in the postoperative care of these anatomically and microbiologically challenging wounds. A central effect of incisional NPWT in inguinal or other lower limb incisions could simply be to provide a high-quality protective cover to the healing wound for a seven-day period. The constant suction that is being applied by the incisional NPWT-system provides a highly-adaptive surface that prevents kinking of the wound edges and a subsequent breach of the sterile barrier resulting in bacterial contamination during movements of the hip joint.

Only elective procedures will be included. This is primarily due to ethical concerns in including patients in need of an emergency operation. Previous surveys using a validated wound infection register found a 4% SSI rate after emergency operation and 27% SSI rate after elective vascular procedures [22]. This much higher SSI rate after elective vascular surgery has been speculated to be a consequence of poor patient environment, hygiene facilities and routines at the ward for vascular surgery patients prior to surgery.

A potential limitation of this study could be that the randomization takes place before the operation, not at its end. One might argue that this could create bias since the surgeon in charge, could be aware of the respective randomization outcome before conducting the operation and thereby subconsciously or consciously modify their behavior and surgical technique. Because of the large staff turn-over in the operation room, an intraoperative randomization would most likely have led to a very large number of patient dropouts due to insufficient sense of awareness for the study and the principal investigator felt that intraoperative computer-generated randomization not seems feasible. Use of randomization envelopes in the operation room was not felt as an option either due to issues of management of these envelopes and the large turnover of personnel at present times. When wound closure has been performed, the surgeon usually leaves the operation room and the scrub nurse finalizes the wound care including application of wound dressings. That is usually the time to take a look at the randomization results in the patient files, which should minimize bias due to behavior issues. At present time, four vascular centers will be enrolling patients into the study and these centers does not, for instance, have identical perioperative wound care. The type of standard wound dressing used in the control arm might differ. We will, however, document the type of wound dressing and perform sub analysis accordingly. Generalizability of the results will be better in a multi-centre trial including both university hospitals and county hospitals.

Prospective RCT studies are prone to the Hawthorne effect, leading to changes in behavior among personnel and patients [23]. This may affect the results in both the interventional and control arms of this study. To address this issue a parallel qualitative study was initiated in Jönköping. The aim of this randomized controlled trial is to provide more high-quality evidence as to the effects of incisional NPWT after vascular surgery with groin and lower limb incisions, in particular TEA and lower limb bypass. To avoid bias, the authors have decided to publish the rationale and methods of this study, especially the sample size calculation, prior to enrollment completion and analysis. The results of the trial could not only be important for postoperative wound management in vascular patients, but could be relevant to other specialties conducting operations with incisions at high risk of SSI.

